#### Implementation evaluation: direct and indirect outcomes

For the implementation science component of the study we will measure coverage, adoption, and fidelity of SDR implementation using survey, administrative, and program data on activities and outputs. We will track indicators on program reach (e.g. percentage of primary care clinics where women are routinely advised to deliver at delivery hubs; percentage of women who report being advise to deliver in delivery hubs); adoption (e.g. percentage of women delivering at delivery hubs; percentage of delivering at health centers; labor and delivery quality of care; ANC and PNC utilization and quality; C-section rate); and intervention fidelity (maternity ward and newborn unit expansions in delivery hub hospitals; specialist physician and nurse staffing levels; maternity and newborn staff knowledge levels; availability of critical inputs such as blood for transfusions).

Given the size and scope of the policy reform, it is likely that SDR will affect the health system in indirect ways, beyond the hypothesized effects on maternal and newborn health services. Complex system-level reforms can have both positive and negative broader systemic effects. Therefore we will measure potential system-level effects of SDR as secondary implementation outcomes (Table 1).

**Table 1 Tab1:** Implementation evaluation indicators

Direct effects: Implementation evaluation		
Reach	% ANC clinics where women are routinely advised to deliver at delivery hubs	Primary care facility survey
	Percentage of women who report being advised to deliver in delivery hubs	Longitudinal survey
Adoption	% women delivering at delivery hubs	Pregnancy registry; KHIS
	% women delivering at primary care facilities	Pregnancy registry; KHIS
	Delivery quality of care	Delivery observation checklist
	ANC and PNC utilization	Pregnancy registry; KHIS
	Caesarean section rate	Pregnancy registry; KHIS
Fidelity	Maternity ward and newborn unit capacity in delivery hub hospitals	Delivery hub survey
	Maternity and newborn staff knowledge levels	Delivery hub and primary care provider assessments
	Availability of critical inputs (e.g. blood for transfusions)	Delivery hub facility survey
	Specialist physician and nurse staffing levels	Delivery hub facility survey
Indirect effects: Implementation evaluation		
Indirect effects	Utilization for non-MNCH services (e.g. HIV, TB) from hospital congestion	KHIS
	Utilization of private sector for deliveries	KHIS; Pregnancy registry
	Continuity of ANC, delivery, and post-natal care	Pregnancy registry
	Surgical volumes for non-MNCH conditions	KHIS
	Health worker morale and retention	Delivery hub and primary care provider assessments
	Delivery hub congestion/overcapacity	KHIS

*MNCH:* Maternal, Newborn and child health, HIV: Human Immunodeficiency virus, *TB:* Tuberculosis

### Power calculations

For the impact evaluation evaluation component, we performed simulation-based power calculations for the composite outcome in the stepped wedge evaluation design to determine the number of facilities to sample. We excluded private facilities, facilities in Kakamega town, and facilities with less than or equal to 6 first antenatal care visits per month. There were 94 facilities in control sub-counties and 59 in treated sub-counties.

We assumed that the baseline composite outcome was 0.0406. Given that direct observation of the primary composite health outcome was not available at baseline, we estimated it using three strategies and selected the most conservative estimate (40.6 events per 1000 births) based on a prospective cohort study of maternal death, stillbirth and neonatal deaths with a site in Western Region of Kenya encompassing 31,118 births [17]. We then generated outcome data across Kakamega’s health facilities by:1$$logit\left(P\left({Y}_{ik }= 1 \right| trt, {\gamma }_{0k }\right)= {\beta }_{0}+ {\beta }_{1}{trt}_{ik}+ {\gamma }_{0k }$$

where *k* indicates sub-county, *Y* is composite outcome occurrence for delivery *i* in for a women living in sub-county *k* and *trt* takes value 1 or 0 depending on if the cluster is receiving the intervention during that phase. We also include a random intercept $${\gamma }_{0k}$$ for each sub-county drawn from a normal distribution with standard deviation 0.20, which was based on an assessment of expected variation in composite outcome rates between sub-counties.

To determine the appropriate number of facilities to sample, we calculated the power varying the number of facilities sampled from the treated and control sub-counties. We generated 1,000 simulated datasets followed the planned sampling design by first stratifying by sub-county and then sampling facilities with probability proportional to the number of antenatal care visits in 2021. Over the full study (following the stepped wedge design in which all sub-counties ultimately receive the SDR reform), we determined that we would have 89% power to detect a 12.5% reduction in composite outcome (a drop from 0.0406 at baseline to 0.0355) for 72 facilities, roughly corresponding to 60,000 births. To optimize power in the difference-in-difference Phase 1 study, we determined that equal allocation of 36 facilities in Phase 1 sub-counties and 36 facilities in Phase 2 and 3 sub-counties (18 facilities in Phase 2 and 18 facilities in Phase 3 sub-counties) would result in 86% power to detect a 30% reduction in composite outcome (with 72% power to detect a 25% reduction). For our secondary outcome of satisfaction, we determined that 2,000 women from the longitudinal study sample would result in > 80% power to detect a 0.15-standard deviation increase for both evaluation designs.

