**Fig. 3 Fig3:**
[figure not shown]
Participant flow diagram

In each sampled facility, survey firm staff working with the research team seeks to enroll all pregnant women who present for antenatal care over a two year period (6 months of baseline and 18 months of implementation).^1^ Based on administrative data from 2021, we estimate that this sampling strategy will yield a sample of 59,753 mothers across the 72 facilities over two years. Approximately 98 percent of pregnant women in Kakamega County receive at least one ANC visit (National Bureau of Statistics et al. 2015). The approximate annual number of births in Kakamega County is 61,442, so over the two years of data collection approximately half of all pregnant women will be enrolled in the study. Any woman who reports that she intends to give birth outside at Kakamega County at the time of enrollment will be excluded. In addition, women who state upon enrollment that they have already made firm plans to deliver at a referral facility due to complications or previous caesarean sections will be excluded. Finally, all pregnant women below 15 years of age will also be excluded.

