### Analysis

#### Full SDR evaluation, primary analysis

The primary analysis will assess the impact of SDR on the composite outcome comprised of maternal mortality, neonatal mortality, and stillbirth. We will perform both an intention to treat and per protocol analysis.

Intention to treat analysis: We will fit the model in Eq. (1), as well as analogous linear models. A participant’s treatment status will be determined based on her sub-county of residence. If she lives outside of Kakamega County, it will be determined by the location of the facility where she is enrolled. Since the order in which subcounties were selected for SDR was not random, but rather was a decisions taken by Kakamega County policymakers, it is possible that respondents will differ on observable characteristics which may be correlated with the study’s outcomes of interest. We will account for sources of confounding by controlling for mother's education, age, parity, transport time to nearest delivery hub, season of pregnancy, and perceived pregnancy risk in our regression model. Self-reported pregnancy risk is captured by the following question “How concerned are you about complications during this pregnancy?” with a response scale of 1 (no concern) to 5 (very concerned) and will be coded as a binary variable indicating high risk (choice of >  = 4). Distance will be measured by approximate travel time from a woman's village to the delivery hub. Additional confounders from external data sources such as rainfall or temperature data may be incorporated in the model, depending on availability.

Per protocol analysis: We will compute the proportion of women living outside of intervention areas that are delivering at another sub-county's updated delivery hub. If this happens often (> 5% of deliveries in non-intervention facilities), we will also estimate the effect of delivery in an updated delivery hub on the composite outcome (instead of the effect of living in a treated sub-county). In addition to the confounders listed for the intention-to-treat analysis, we will adjust for whether the woman comes from an intervention area.

Account for missing outcomes data: We expect there to be loss-to-follow-up after delivery resulting in missing values for the composite outcomes. The survey team will attempt multiple phone-based and in-person tracking options before coding an outcome as missing. We will use multiple imputation to impute missing outcome values.

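### The 89% power for a 12.5% reduction is reported from a model with no calendar-time term; with period effects the same design has roughly 25–45% power, about 40% at equal 6-month steps

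*Protocol article*

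**What the plan says.** Under Power calculations, the authors simulate 1,000 datasets to choose the number of facilities. The baseline rate is fixed: "We assumed that the baseline composite outcome was 0.0406". The data come from Eq. (1), a logistic model with an intercept, a treatment indicator and a sub-county intercept "drawn from a normal distribution with standard deviation 0.20". It has no period or trend term. The result for the full stepped-wedge evaluation is that "we determined that we would have 89% power to detect a 12.5% reduction in composite outcome", described as "a drop from 0.0406 at baseline to 0.0355", "for 72 facilities, roughly corresponding to 60,000 births". For the Phase 1 difference-in-difference study, 36 facilities in Phase 1 sub-counties and 36 elsewhere (18 in Phase 2, 18 in Phase 3) "would result in 86% power to detect a 30% reduction in composite outcome", with 72% power for a 25% reduction.

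Under Full policy evaluation, groups of 3, 4 and 5 sub-counties start in turn, in an order set by county policymakers. Under Participants, enrolment covers 6 months of baseline and 18 months of implementation, and "we estimate that this sampling strategy will yield a sample of 59,753 mothers across the 72 facilities over two years". Under Full SDR evaluation, primary analysis, the planned model is Eq. (1) with maternal covariates and season of pregnancy; no calendar period or secular trend is named. The same section says "We expect there to be loss-to-follow-up after delivery resulting in missing values for the composite outcomes".

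**The concern.** In a stepped wedge the treated share of births rises with calendar time by construction. A comparison that ignores time counts every later-versus-earlier difference as treatment information, which makes the design look far more precise than it is. Once period effects are fitted, only contrasts between sub-counties at different stages in the same period remain, and power falls.

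Secular change is plausible here. The Background section itself cites a global fall in maternal mortality of 2.9% per year. The number of facilities was chosen from these simulations, and 89% is the power reported for that number. If it stands, a null result will be read as evidence against a 12.5% reduction that the design, analysed with allowance for time, has less than even odds of detecting under most assumptions.

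**Working it through.** **Inputs from the article.** Rates 0.0406 and 0.0355; SD 0.20 on the logit scale; 60,000 births; groups of 3, 4 and 5 sub-counties; 24 months with a 6-month baseline; facilities 36/18/18.

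**Assumptions, because the article does not give them.** Alpha 0.05 two-sided; starts at months 6, 12 and 18; births split 50/25/25 in line with the facilities and spread evenly over time.

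**Effect.** Log odds ratio = ln(0.0355/0.9645) − ln(0.0406/0.9594) = −0.1395. Power = Φ(0.1395/SE − 1.96). The SE comes from generalised least squares (Hussey–Hughes type) on sub-county-by-period cells, with cell variance 1/(n·p·(1−p)) plus a shared variance of 0.20² within each sub-county.

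**Step 1: the stated figure, without time.**
- Crude two proportions. Treated share = 0.50×18/24 + 0.25×12/24 + 0.25×6/24 = 0.5625, giving 33,750 treated and 26,250 untreated births. SE = √(0.0355×0.9645/33,750 + 0.0406×0.9594/26,250) = 0.00158. Power = Φ(0.0051/0.00158 − 1.96) ≈ 0.90. With 59,753 births and an exact 12.5% reduction it is 0.89.
- Eq. (1) as written. SE = 0.0467; Φ(2.99 − 1.96) = 0.85. Simulation with a refitted logistic mixed model (2,000 datasets) gives 85.5%.
- Steps 3 to 8 months apart give about 79–86% under Eq. (1). A one-sided test gives 91% at equal steps.

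The stated 89% therefore lies within the range of models that omit time, although Eq. (1) at equal steps and two-sided 0.05 falls about four points short of it.

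**Step 2: the same design with period effects.**

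| Model | SE | Power |
|---|---|---|
| Categorical periods, random sub-county | 0.0798 | Φ(1.75 − 1.96) = 0.42 |
| Categorical periods, fixed sub-county | 0.0826 | Φ(1.69 − 1.96) = 0.39 |
| Linear trend | 0.0740 | Φ(1.89 − 1.96) = 0.47 |
| Categorical periods, one-sided 0.05 | 0.0798 | Φ(1.75 − 1.645) = 0.54 |

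Simulation of the first row gives 43.0%.

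**Step 3: sensitivity.**
- Steps 3 to 8 months apart: 28–45% with categorical periods. The least favourable calendar in a wider grid with a 6-month baseline gave 25%.
- Across step spacings: a linear trend reaches about 50%; a one-sided test with categorical periods reaches about 57%.
- Linear trend and one-sided test together at equal steps: Φ(1.89 − 1.645) = 0.60.
- Birth splits from 40/30/30 to 60/20/20: 39–43%.
- SD near 0 with the most favourable calendar, which departs from the article's own 0.20: 72%.

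**Step 4: detectable reduction with categorical periods at equal steps.** For a 20% reduction, log odds ratio −0.2316 and SE 0.0814: Φ(2.85 − 1.96) = 0.81. For 22% the power is 0.88, so about 20% is detectable with 80% power and about 22% with 89%.

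**Step 5: Phase 1 cross-check.** 6 months before and 6 after, about 30,000 births.

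| Model | 30% reduction | 25% reduction |
|---|---|---|
| Stated | 86% | 72% |
| With a period effect (fixed to random sub-county) | 85–89% | 69–75% |
| Without a period effect | 99% | 93% |

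**Step 6: what omitting time does to the test.** With no true effect and a fall of about 4% in the odds per 6 months, the model without time rejected in 41.5% of 600 simulated datasets, against 5.0% with period effects.

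**Step 7: loss to follow-up.** With period effects, 54,000 births (10% lost) give 38% and 48,000 (20% lost) give 35%, against 42% with none lost: about 3 to 7 points.

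**The case against.** The strongest reply is that this is not faulty arithmetic. The article simulates from Eq. (1) and says it will fit Eq. (1), so its power figure is consistent with its stated analysis, and the real defect is the missing time term in that model. That stands as a description of the cause, but it does not save the figure. If an analysis plan not shown here adds period terms, 89% is not the power of that analysis. If it does not, treatment is confounded with any secular trend. The planned adjustment for season, and possibly for rainfall or temperature, does not remove a trend; season terms alone lower the no-time power to about 78%.

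Four stronger readings are tempting, and the article does not support them.

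- A reader might infer that the true power is 40%. That value rests on assumed step dates, alpha, sidedness and birth shares; the defensible statement is a range.
- A reader might infer that the origin of the 89% has been established. Eq. (1) gives about 84–86% at equal steps, and the article does not say which model was fitted to the simulated datasets.
- A reader might infer that the Phase 1 figures prove the two powers rest on different models. The match is suggestive only. A difference-in-difference contains a period contrast by construction, the article says the designs differ, and a no-period model counting only 2 to 3 months of post-period births would also bracket 86% and 72%.
- A reader might infer that refusals and exclusions were ignored. The 59,753 is presented as the expected yield and may already be net of them; the article does not say.

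**Conclusion.** The concern holds. The 89% is reported from simulations under a model without calendar time, for a design in which treatment and time move together and the order was not randomised. With period effects, SD 0.20, two-sided 0.05 and a 50/25/25 split, power for a 12.5% reduction is about 40% at equal 6-month steps and about 25–45% over other step dates. No time-adjusted variant tried at SD 0.20 approaches 89%; the most lenient, a one-sided test with a linear trend, gives 60% at equal steps. The reduction detectable with 80% power is about 20% rather than something near 12.5%.

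The loss-to-follow-up point is secondary. The births used match the expected number of mothers, with no visible deduction for the loss that the article anticipates. It is worth a few points against a gap of more than 40 points at equal steps.

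**What to change.** Re-run the existing simulation with period effects in the fitted model, the planned step dates, and births net of the expected loss to follow-up. State alpha and sidedness. Replace the 89% statement with the result of that re-run and the reduction detectable at 80% power; where step dates are uncertain, give the range over plausible calendars. Say explicitly how time is handled in both the stepped-wedge and the Phase 1 power figures, so that a reader can see whether they are comparable. The primary analysis model should carry the same period terms, since otherwise the restated power would describe an analysis that is not planned.

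The cost is a re-run of existing code and a less favourable stated figure. No extra enrolment is needed.

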#### Full policy evaluation

This study will use a prospective, observational stepped wedge design. Kakamega County is planning to implement a phased rollout of SDR by sub-county, in three phases. Kakamega has 12 sub-counties: the reform will be implemented first (starting in 2022) in a group of 3 sub-counties. After a period of implementation in these “phase 1'' sub-counties, a second set of 4 sub-counties will implement the reform. After another period of implementation in these phase 2 sub-counties, a final set of 5 sub-counties will implement the reform (Fig. 2). This phased approach parallels the structure of a stepped wedge trial in that delivery and post-delivery outcomes for mothers and newborns can be compared within each group of sub-counties that implement SDR in the same implementation phase before and after the roll-out, as well as across counties in the same phase of rollout. Analytically, the analysis is also similar to that of a stepped wedge cluster randomized trial; the difference is that the order in which the clusters are exposed to treatment was decided not via randomization, but was decided by Kakamega County policymakers.

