#### Secondary analyses

Secondary outcomes include satisfaction with care, respectful care index, out-of-pocket expenditures, location of delivery, travel time, maternal complications, and equity. These outcomes will be analyzed as above, with the exception the respectful care index and travel time outcomes, which will be restricted to the random sample of women in the longitudinal cohort. We will also analyze equity for selected outcomes (e.g. quality of care, OOP cost). In this analysis we will include an interaction term between delivering at an updated delivery hub and the equity markers to assess baseline disparities in outcomes and test if these disparities changed during the intervention.

Phase 1 interim analysis: After six months of data has been collected following the implementation of improvements in Phase 1, we will conduct a study on interim outcomes to understand implementation of the reform and how it has affected women's decision-making about delivery care. We will examine the effect of policy exposure on the same outcomes as in the full evaluation. The main analytical difference is that this analysis will be conducted using a difference-in-difference design rather than a stepped-wedge design as we will only observe the intervention among women living in Phase 1 sub-counties. Otherwise, the analytical approach will be the same for the Phase 1 study as for the full SDR evaluation.

Data collection will be monitored in an ongoing basis using the interim analysis described in Additional file 1: Appendix 1.

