### Strengths and limitations

This study has a number of strengths, including its prospective stepped-wedge design, large sample, and detailed measurement of the pathways by which the health outcomes may be affected. However, there are several limitations to consider. First, the reform is not randomized; the order of phased implementation was determined by the Kakamega County Department of Health team to maximize synergy with planned facility upgrades and other interventions. Second, implementation in the second and third phases of sub-counties is not assured and depends on additional financing and County commitment following Kenya’s 2022 elections. We account for this with the secondary difference-in-differences study design nested within the larger study. Third, as the sub-county is the natural administrative level for the intervention, there are a limited number of study clusters. Finally, the reliance on self-reported health outcomes may lead to measurement error in event rates. We plan to validate these self-reported health outcomes with facility records for a subset of women who deliver in a health facility to address this concern.

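### With 3 treated and 9 comparator sub-counties, the Phase 1 model takes its precision from birth counts alone; intervals should rest on the 12 sub-county changes, and the basis of the 86%/72% power should be stated

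*Protocol article*

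**What the plan says.** Service Delivery Redesign is rolled out by sub-county. Under Full policy evaluation, "the reform will be implemented first (starting in 2022) in a group of 3 sub-counties", then "a second set of 4 sub-counties will implement the reform", then "a final set of 5 sub-counties will implement the reform". Phase 1 is therefore a contrast of 3 treated with 4 + 5 = 9 comparator sub-counties. Under Power calculations, the sample is an "equal allocation of 36 facilities in Phase 1 sub-counties and 36 facilities in Phase 2 and 3 sub-counties", chosen to optimise Phase 1 power.

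Eq. (1) generates the power data and is also the planned analysis model. It is a birth-level logistic model with a treatment term and one random intercept per sub-county (SD 0.20), constant over time. The Phase 1 analysis is a difference-in-difference, and the section on it adds: "Otherwise, the analytical approach will be the same for the Phase 1 study as for the full SDR evaluation".

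The stated result is that this allocation "would result in 86% power to detect a 30% reduction in composite outcome (with 72% power to detect a 25% reduction". No test, alpha, sidedness or length of follow-up is given with these two figures.

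Strengths and limitations concedes that "as the sub-county is the natural administrative level for the intervention, there are a limited number of study clusters", without saying how the analysis will allow for it.

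**The concern.** The policy is assigned to sub-counties, so the Phase 1 effect is a difference between 3 pre-to-post changes and 9. If sub-counties drift apart for reasons unrelated to the reform (staffing, strikes, local programmes, reporting), that drift is part of the error of the estimate. It can be judged only from 12 changes, which leaves about 12 - 2 = 10 degrees of freedom. Eq. (1) has no term for such drift. Its single intercept describes level differences between sub-counties, which the difference-in-difference removes anyway.

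Phases 2 and 3 are not assured. If they do not happen, the same 3-versus-9 comparison becomes the evaluation of the policy. Intervals that treat some 30,000 births as the main source of information could then be too narrow, and a chance divergence between sub-counties could be read as an effect on mortality.

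**Working it through.** **Inputs.** Births: 59,753 over 24 months (Participants), or 59,753 / 24 = 2,490 per month. Baseline: 6 months (Participants). Phase 1 follow-up: 6 months (Secondary analyses). Baseline risk: "We assumed that the baseline composite outcome was 0.0406". Sub-county SD: 0.20. Assumed: two-sided 5%, equal births per facility, and a period term in the difference-in-difference.

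**1. Why the intercept drops out.** On the logit scale a sub-county's change is (β0 + γ0k + period + β1) - (β0 + γ0k) if treated, and the same without β1 if not. γ0k cancels, so its SD of 0.20 adds almost nothing to the variance of the contrast.

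**2. Reproducing the stated power at 6+6 months.** Twelve months give 29,876 births, or 7,469 in each of four cells (treated/comparator by before/after). The variance of the difference-in-difference log odds ratio is the sum over cells of 1 / [n p (1 - p)].

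- 30% reduction: risk 0.0406 × 0.70 = 0.02842 and log odds ratio 0.3693. Variance = 3/(7,469 × 0.0406 × 0.9594) + 1/(7,469 × 0.02842 × 0.97158) = 0.01516, so SE = 0.1231. Ratio 3.00; power Φ(3.00 - 1.96) = 85%.
- 25% reduction: risk 0.03045, log odds ratio 0.2982, variance 0.01485, SE 0.1218. Ratio 2.447; power Φ(2.447 - 1.96) = 69%.

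Simulating 3,000 data sets per setting from Eq. (1), with a birth-level Wald test, gives 87.0% and 70.3%. The stated figures are 86% and 72%.

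**3. The same information judged on 12 changes.** With 10 degrees of freedom the critical value is 2.228 instead of 1.96.

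| Route (no sub-county-by-period variation) | 30% reduction | 25% reduction |
|---|---|---|
| Stated power converted: noncentrality 1.96 + 1.08 = 3.04 and 1.96 + 0.58 = 2.54, noncentral t(10) | 78% | 63% |
| Simulated births-weighted test of the 12 changes, t(10) | 77.8% | 61.0% |
| Simulated exact permutation over the 220 choices of 3 from 12 | 56.7% | 40.5% |

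With an assumed sub-county-by-period SD of 0.10, the births-weighted t(10) test has 63.4% and 46.6% in simulation. Its type I error there is 6.0%, so these figures are slightly generous.

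**4. Type I error of the birth-level test.** Under no effect the birth-level variance is 4/(7,469 × 0.0406 × 0.9594) = 0.01375. A sub-county-by-period SD of τ adds 2τ²(1/3 + 1/9), which the test does not see.

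- τ = 0.05: adds 0.00222. True SE is √(1 + 0.00222/0.01375) = 1.078 times the assumed one; 1.96/1.078 = 1.819; error 6.9%.
- τ = 0.10: adds 0.00889. Factor 1.283; 1.96/1.283 = 1.527; error 12.7%.

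Two simulations agree: 4.8% and 4.9% at τ = 0, 7.1% and 6.3% at 0.05, 13.4% and 12.3% at 0.10. The documents give no value for τ; these are assumed.

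**5. Dependence on follow-up.** With 6 months before and 10 to 11 after, t(10) gives 86-88% and 70-72%. With 6 before and 18 after (the two-year fallback), the ratios are 3.762 and 3.054, and t(10) gives about 92% and 79%.

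**The case against.** The strongest reply is that the test behind the power figures is not stated, and that a condensed article commonly leaves the reference distribution of a mixed model to the analysis plan. That stands as far as it goes. A reader might infer that 86% and 72% can come only from a normal-reference test and are therefore wrong. The documents do not support this: with 10 to 11 months of follow-up a 12-unit t test matches them as well. Under the plan's own generating model, with no sub-county-by-period variation, a large-sample test is valid and the figures are about right.

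A reader might also infer that the fallback evaluation is underpowered. It is not, on the same zero-variation assumption: First phase interim evaluation specifies the full two-year period, for which t(10) gives more power than the stated figures.

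Nor is it fair to say that the model ignores clustering, since Eq. (1) has a sub-county intercept, or that the problem is hidden, since the limited number of clusters is disclosed.

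What remains is not mere missing detail. The article fixes a model for Phase 1 whose precision does not reflect differential change between sub-counties. It also publishes a power figure whose meaning depends on a test and a follow-up length that it does not give.

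**Conclusion.** The concern holds in a limited form. As planned, Phase 1 and fallback intervals are valid only if the 12 sub-counties would have changed in parallel apart from sampling error. At an assumed SD of 0.05 to 0.10 for differential change, a nominal 5% test rejects about 6-7% to 12-13% of the time. If the stated power refers to 6+6 months, a test that respects the 12 units has at best about 78% for a 30% reduction and 61-63% for a 25% reduction, and less with any such variation (about 63% and 47% at SD 0.10). For the two-year fallback the issue is the validity of the intervals, not a power shortfall. All this rests on two-sided 5%, equal births per facility, and an inferred test. It should be corrected, but it does not show that the stated power was miscalculated.

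**What to change.** For the Phase 1 and fallback difference-in-difference, take confidence intervals and p-values from the variation between the 12 sub-county changes, with a t reference on about 10 degrees of freedom. Use a matching small-sample correction in the 12-cluster stepped-wedge analysis. Adding a sub-county-by-period variance while keeping a normal reference would not be enough: simulated type I error was still 7.1% at SD 0.10.

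Permutation over the 220 allocations should not be offered as an equivalent option. Sub-counties contribute very different numbers of births (36 facilities over 3 against 36 over 9), assignment was not random, and power falls to about 57% and 40%.

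In Power calculations, state the test, alpha and follow-up length behind 86% and 72%. If they refer to 6+6 months, restate them as at best about 78% and 61-63%, and say that they fall with any sub-county-by-period variation.

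The cost is wording, wider intervals and a less favourable stated power. No further data are needed.
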